### Statistical analysis

We will not conduct subgroup or adjusted analyses of the trial. The independent statistical analysts will be responsible for the data analysis. All patients will be analysed on the basis of intent-to-treat analysis, including all randomized subjects who take Baidu Jieduan granules at least once and have follow-up information recorded. In the case of missing data, multiple imputation will be carried out to generate missing values. A per-protocol analysis, which includes patients who completed the trial without conflict with the major protocol, can be conducted as appropriate. Then, the statistician will submit statistical reports in a timely manner to the study director. The statistical analysis will be performed in a blinded manner using SPSS 20.0 software. Continuous variables characterizing each study group will be expressed as the mean with standard deviation or median with interquartile range. Categorical variables will be reported as frequencies and proportions. Continuous outcomes will be analysed by unpaired Student’s *t*-test or Wilcoxon’s nonparametric statistic, while count data will be compared using a chi-square test or Fisher’s exact test. All statistical tests will be two-sided. *P* < 0.05 will be considered statistically significant. We will not carry out an interim analysis.

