### Sample size

A similar clinical trial has been conducted using TCM to decrease the rate of symptoms (fever, fatigue and coughing) in patients with COVID-19 [14]. The rate of recovery of clinical symptoms was 91.2% in patients who received TCM treatment and 61.1% in patients who received conventional treatments. Considering 90% power with a significance level of 10%, as well as a rate of withdrawal and loss to follow-up of 10% [15], we plan to recruit at least 150 participants in each group to achieve sufficient precision in a subsequent full trial.

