### Randomization and blinding

The enrolled participants will be randomly assigned to the Baidu Jieduan granule group or the conventional treatment group according to random codes. The random sequence of 300 participants from 4 medical centres will be generated by SPSS 19.0 and stratified by centre. Two sets of random codes will be stored in opaque envelopes, which will be sent to the research sponsor and each of the centres. Thereafter, the drug administrators will arrange the nurse to dispense the study drug in the order of random numbers. This will be an open-label study. The statistical analysis will be carried out by the Professors of Statistics of Shanghai University of Traditional Chinese Medicine, who will be blinded to the patient allocation.

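### Randomization is stratified by centre but adjusted analyses are ruled out, which costs power if outcome rates differ substantially between centres

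*Protocol article*

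**What the plan says.** Under Randomization and blinding, the article states: "The random sequence of 300 participants from 4 medical centres will be generated by SPSS 19.0 and stratified by centre". Centre is the only stratification factor named. No block scheme is described.

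Under Statistical analysis, it states: "We will not conduct subgroup or adjusted analyses of the trial". The tests named there are the unpaired t-test or Wilcoxon test for continuous outcomes and, for binary outcomes, "count data will be compared using a chi-square test" or Fisher's exact test. The section also says "All statistical tests will be two-sided", with significance at 0.05. No section provides a test that uses centre.

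The primary outcome under Outcomes and measurements is binary: the proportion with a negative nucleic acid result on day 14. The Sample size section rests on a different outcome: "The rate of recovery of clinical symptoms was 91.2% in patients who received TCM treatment and 61.1% in patients who received conventional treatments".

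**The concern.** The design uses centre to form the allocation, and the analysis then discards it. When outcome rates vary by centre, part of the outcome variance lies between centres. A stratified test removes that part from the comparison, while a plain chi-square test leaves it in the standard error. The trial then gives up power that the design could have delivered.

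The article does not leave this open for an analysis plan to settle. It rules adjustment out, so a later plan with a centre-stratified test would contradict the published protocol.

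Centre differences are plausible. The sites are a university hospital, a Wuhan hospital and two traditional Chinese medicine hospitals, and the inclusion criteria admit ages 18 to 85 without a severity criterion. The article gives no outcome rates by centre, so the size of any difference is unknown.

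**Working it through.** **Inputs from the article.** Four centres, 1:1 allocation, 300 patients, 10% withdrawal and loss to follow-up, two-sided 5% tests. Evaluable per arm: 150 × 0.9 = 135.

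**Assumptions.** Control rates by centre, four centres of nearly equal size (34/34/34/33 per arm) and a common odds ratio of 2. The article gives none of these.

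**1. The article's own figure.** For 0.912 v 0.611, with two-sided alpha 0.10 and 90% power,

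n = [z(α/2)·√(2p̄q̄) + z(β)·√(p₁q₁ + p₂q₂)]² / (p₁ − p₂)²

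gives 33 per group, or 33/0.9 → 37 after dropout. The stated 150 is not reproduced. That is a separate matter; here it means only that 135 evaluable per arm is far more than this effect needs. The odds ratio is (0.912/0.088)/(0.611/0.389) ≈ 6.6. At this effect, with about 136 per arm, the chi-square and CMH tests both exceed 99.9% power in every centre scenario tried.

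**2. Size of the unstratified test when arms are balanced within centre.** Let r be the mean within-centre variance divided by the total variance:

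r = mean[pᵢ(1 − pᵢ)] / [p̄(1 − p̄)], actual size = 2·[1 − Φ(1.96/√r)]

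- 50/65/80/90%: within = (0.25 + 0.2275 + 0.16 + 0.09)/4 = 0.1819; total = 0.7125 × 0.2875 = 0.2048; r = 0.888; size ≈ 3.7%.
- 40/60/80/95%: within = (0.24 + 0.24 + 0.16 + 0.0475)/4 = 0.1719; total = 0.6875 × 0.3125 = 0.2148; r = 0.800; size ≈ 2.8%.
- 70/75/75/80%: within = (0.21 + 0.1875 + 0.1875 + 0.16)/4 = 0.1863; total = 0.75 × 0.25 = 0.1875; r = 0.993; size ≈ 4.9%.

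**3. Simulation at odds ratio 2** (60,000 or more replicates per scenario; repeat runs agree to within about half a point). Chi-square v CMH:

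| Control rates by centre | Allocation within centre | Type I error | Power |
|---|---|---|---|
| 75% in all four | balanced | no material difference | 60.9% v 60.5% |
| 70/75/75/80% | balanced | chi-square about 5% | 60.6% v 60.4% |
| 65/70/80/85% | balanced | chi-square 4.7% | 59.2% v 59.9% |
| 50/65/80/90% | balanced | 3.7% v 4.8% | 58.6% v 61.9% |
| 40/60/80/95% | balanced | 2.9% v 4.9% | 54.6% v 61.8% |
| 50/65/80/90% | simple | chi-square about 5% | 57.9% v 61.4% |
| 40/60/80/95% | simple | chi-square about 5% | 53.8% v 60.9% |

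The power loss in the two wide-spread scenarios is 61.9 − 58.6 = 3.3 and 61.8 − 54.6 = 7.2 points with balance. With simple randomization it is 61.4 − 57.9 = 3.5 and 60.9 − 53.8 = 7.1 points. So the loss of power does not depend on blocking, whereas the fall in type I error does.

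**4. A second set of assumptions** (control rates averaging about 0.61, log odds ratio 0.8, 74 patients per centre, balanced). Power, chi-square v CMH, is 87.6% v 87.7% for rates of 0.55 to 0.65, 85.5% v 86.6% for 0.45 to 0.76, and 74.7% v 81.1% for 0.30 to 0.90. The pattern is the same.

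**The case against.** A prespecified unadjusted comparison is valid. It does not bias the estimate or raise the false-positive rate, and ruling out adjustment guards against data-driven models in an open-label trial. All sites share eligibility criteria and one national treatment protocol, so centre differences may be small. At the article's assumed effect the choice of test makes no difference to power.

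Much of this stands. It limits the point to efficiency and makes its size conditional. Three stronger readings that a reader might infer should be set aside:

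- *Power is lost whenever centres differ.* The calculations show no loss at 70/75/75/80% and 0.7 points at 65/70/80/85%. A material loss needs a wide spread.
- *Type I error falls below 5%.* This requires balance within centre. Stratified randomization usually aims at that through blocks, but the article says only that the sequence "will be generated by SPSS 19.0 and stratified by centre". With simple randomization within each centre, size stays near 5%.
- *Large centre differences are likely.* The mix of hospitals makes them plausible, but the article has no figures to show them.

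Two parts of the objection do not carry through. The power above 99.9% belongs to symptom recovery, whereas the primary outcome under Outcomes and measurements is nucleic acid negativity, for which no effect is assumed. (The Abstract names symptom recovery as primary; that conflict is a separate matter, and the point here applies to either binary outcome.) Also, a test stratified by the one factor used in the randomization is fixed by the design, so it opens no door to data-driven adjustment.

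**Conclusion.** The point holds as one of efficiency. The article stratifies by centre and then forbids the analysis that would use the stratification. The cost is about 3 to 7 points of power with control rates spread over 40 to 55 percentage points, and essentially nothing when centres are alike. Conservatism, with type I error of about 3 to 4% in those scenarios, follows only if allocation is blocked within centre. There is no bias and no inflation of false positives. These sizes rest on assumed centre rates, an assumed odds ratio of 2 and nearly equal centre sizes. The change is worth making because the stratified test costs at most a few tenths of a point of power when centres do not differ.

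**What to change.** Replace the sentence that rules out subgroup and adjusted analyses with:

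> Binary outcomes, including the primary outcome, will be compared with a Cochran-Mantel-Haenszel test stratified by centre, with a centre-stratified risk difference and 95% CI. Continuous outcomes will be compared with a linear model including centre or a centre-stratified Wilcoxon (van Elteren) test, and any time-to-event test will be stratified by centre. No other adjusted or subgroup analyses are planned.

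This takes a short replacement passage and no new data, since centre is known for every randomized patient. The CMH test is available in the planned software; availability of the van Elteren test and the stratified risk difference should be checked. Because the trial is open-label, the change should be fixed in writing before outcomes are compared by arm. State at the same time whether allocation is blocked within centre.

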### Outcomes and measurements

The primary outcome will be the proportion of negative SARS-CoV-2 nucleic acid results on the 14th day. The secondary outcomes will be the time to symptom recovery, the proportion of cases with reversion on chest CT, the time to negative SARS-CoV-2 nucleic acid results and the proportion of participants regrouped as severe cases. Symptom recovery is defined as the complete disappearance of fever, fatigue and coughing symptoms.

Evaluation of the primary and secondary outcomes will occur at five points (before treatment and the 3rd, 5th, 7th and 14th days of hospitalization).

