### Safety outcomes

All safety-related indexes, including vital signs, complete routine blood indexes, routine general urine indexes, biochemical indexes, faecal occult blood test results and electrocardiogram results, will be tested and recorded in the CRF at every visit. The biochemical test includes C-reactive protein, hepatic function indicators (alanine transaminase, aspartate transaminase, alkaline phosphatase, total bilirubin and gamma-glutamyltransferase) and renal function indicators (blood urea nitrogen and serum creatinine). Any AE will be evaluated by a professional researcher at each visit and recorded on the CRF.

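### The ban on adjusted analyses is valid, but it forgoes a modest, assumption-dependent gain in power where no planning rate is given and leaves no prespecified answer to chance imbalance

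*Protocol article*

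**What the plan says.** The Statistical analysis section states "We will not conduct subgroup or adjusted analyses of the trial". For binary outcomes it specifies that "count data will be compared using a chi-square test or Fisher’s exact test", and the threshold is given by "All statistical tests will be two-sided. *P* < 0.05 will be considered statistically significant". No model with covariates appears anywhere.

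The same article describes baseline data that a model could use:

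- Outcomes and measurements: "Evaluation of the primary and secondary outcomes will occur at five points", the first of them before treatment. Symptoms and chest CT are therefore assessed at baseline.
- Safety outcomes: "The biochemical test includes C-reactive protein", and the panel goes on the case report form at every visit.
- Inclusion criteria: age is known at entry and runs from 18 to 85.
- Randomization and blinding: the sequence is stratified by centre, with four centres.

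The Sample size section gives one pair of rates: "The rate of recovery of clinical symptoms was 91.2% in patients who received TCM treatment and 61.1% in patients who received conventional treatments". From these, "we plan to recruit at least 150 participants in each group". No rate is given for nucleic acid negativity on day 14 (the primary outcome in the Outcomes section), for CT reversion or for regrouping as severe.

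**The concern.** This is a stated choice, not detail left to a separate analysis plan: a plan that adjusted would contradict the protocol. Three things make the choice unattractive.

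1. Baseline status is built into two outcomes. Symptom recovery means that fever, fatigue and coughing have all gone, and the listed entry criteria require neither symptoms nor an abnormal CT. A patient without symptoms at entry already meets the recovery definition, and a normal CT has nothing to revert.
2. The ban also covers centre, so the analysis cannot reflect the factor on which randomization was stratified.
3. If the arms differ by chance in age or illness at entry, any adjusted answer would be post hoc.

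At stake are some power on outcomes that have no planning rate, and how convincing the result is after a visible imbalance.

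**Working it through.** **Step 1: the plan's own figure.** Inputs from the Sample size section: p1 = 0.912, p2 = 0.611, power 90%, alpha 10% (sides not stated), dropout 10%, 150 per group.

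n = [z(α/2)·√(2·p̄·q̄) + z(β)·√(p1q1 + p2q2)]² / (p1 − p2)²

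- p̄ = 0.7615, so √(2·0.7615·0.2385) = 0.6027.
- √(0.0803 + 0.2377) = 0.5639.
- Two-sided alpha 0.10: (1.645·0.6027 + 1.282·0.5639)² / 0.301² gives 33 per arm, and 33/0.9 gives 37.
- Two-sided alpha 0.05: 41 per arm, 46 after dropout.

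The stated 150 is not reproduced. That is a separate matter, but it explains the next result.

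**Step 2: power at the planning rates, two-sided 0.05.**

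- 150 per arm: (0.301·√150 − 1.96·0.6027)/0.5639 = 4.44, power 0.999996.
- 135 per arm (150 less 10%): 4.11, power 0.99998.

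Simulated power with and without adjustment is about 1.00 here, so there is no gain.

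**Step 3: smaller effects (all assumed).** Simulation of 2,000 trials per scenario, 150 per arm, with one standard-normal baseline index in a logistic model. The coefficient is the log odds ratio per SD. Entries are unadjusted → adjusted power, %.

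| Coefficient (AUC) | 61.1 v 77 | 70 v 84 | 80 v 91 |
|---|---|---|---|
| 0 (useless) | 86.9 → 86.4 | 83.6 → 83.0 | 78.8 → 78.6 |
| 0.5 (about 0.64) | 84.4 → 85.9 | 82.8 → 84.5 | 79.2 → 79.5 |
| 0.8 (about 0.70) | 85.0 → 89.6 | 82.7 → 86.1 | 78.9 → 81.7 |
| 1.3 (about 0.79) | 85.9 → 92.4 | 83.4 → 89.6 | 79.7 → 86.0 |

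Gains are 0.3–1.7, 2.8–4.6 and 6.2–6.5 points; the cost of a useless index is 0.2–0.6. Monte Carlo error of a single power is about √(0.85·0.15/2000) = 0.8 points.

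A repeat at 150 per arm with three separate covariates in place of one index gave gains of about 1, 1–3 and 6–9 points at the same coefficients, and a cost under 1 point.

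**Step 4: the same at 135 evaluable per arm** (4,000 runs, coefficients 0.5, 1.0 and 1.5, R² about 0.06, 0.17 and 0.27 at the first pair of rates).

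| Rates, % | 0.5 | 1.0 | 1.5 |
|---|---|---|---|
| 61.1 v 76 | 76.0 → 77.5 | 75.1 → 82.0 | 74.9 → 86.1 |
| 80 v 92 | 82.0 → 82.3 | 82.1 → 85.6 | 82.8 → 89.8 |

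The top gain of about 11 points needs a covariate stronger than any in Step 3. The approximation n/(1 − R²) agrees: at 61.1% v 76%, power is 0.754, 0.797, 0.842 and 0.886 for R² of 0, 0.10, 0.20 and 0.30.

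**Step 5: chance imbalance under no effect** (61.1% in both arms, 135 per arm). Overall, the unadjusted type I error is about 0.04 to 0.06. In the roughly 5% of trials where the covariate favours treatment by more than 0.2 SD, it is 0.07, 0.12 and 0.19 at coefficients 0.5, 1.0 and 1.5, against 0.02, 0.05 and 0.06 adjusted. Each subset has about 190 runs, so these figures carry an error of about 1 to 3 points.

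**The case against.** A reader might infer that the planned analysis is invalid or biased. The documents do not support that. A prespecified unadjusted comparison of randomized arms holds its type I error overall, as Step 5 shows; the inflation appears only in trials selected for an imbalance.

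A reader might also infer that the ban leaves the trial short of power. At the protocol's only stated effect it does not. The effects in Step 3 (15.9, 14 and 11 points) are 53%, 47% and 37% of the planned 30.1 points, and none of them is in the article. Even at 61.1% v 85%, unadjusted power with 150 per arm is about 99.8%. This stands for symptom recovery. It does not carry over to the three binary outcomes without a planning rate.

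Other objections that stand:

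- No prognostic strength is given for any covariate.
- For nucleic acid negativity, everyone enters positive, so the baseline value of that outcome is constant. Any gain would have to come from age, C-reactive protein, symptoms or centre, and the article does not show that these predict clearance.
- Adjustment does nothing about open-label bias, and chance imbalance does not depend on blinding.
- A logistic model may be fragile for regrouping as severe. If 5% convert (assumption), there are 0.05·300 = 15 events for seven terms (arm, three centre indicators, age, C-reactive protein, symptoms), about two per term.
- The one-index simulations contain no centre term, so they do not test the full proposed model.

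**Conclusion.** The point holds as an efficiency and robustness improvement, not as an error. The planned test is valid, and at 61.1% v 91.2% nothing is lost.

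For outcomes without a planning rate, and if true effects are about half the planned one or less, a short prespecified covariate model at 150 per arm would gain about 0–2 points of power with weak covariates, about 1–5 with moderate ones and about 6–9 with strong ones. It would cost under 1 point if the covariates are useless. These ranges rest on assumed effects and assumed covariate strength.

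Two parts do not depend on those assumptions: the analysis is barred from reflecting the factor used to stratify randomization, and there is no prespecified answer to a chance imbalance. The case from baseline status is strongest for symptom recovery and CT reversion, and weakest for nucleic acid negativity.

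**What to change.** Replace the sentence in the Statistical analysis section as follows.

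- **Main analysis of the binary outcomes:** logistic regression on arm, centre, age, baseline C-reactive protein and number of baseline symptoms (0 to 3), plus baseline CT status for CT reversion.
- **Reporting:** the standardized difference in proportions with its 95% CI. Keep the unadjusted chi-square result as supportive.
- **Regrouping as severe:** keep the unadjusted or Fisher's exact test if events are few, with the event count that triggers this stated in advance.
- **Subgroups:** keep the statement that none will be analysed.
- **Timing:** fix the covariates and their coding before the blinded statisticians see allocation. If outcome data by arm have already been examined, the adjusted result can only be supportive.

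Cost: a little more analysis work, simple imputation of any missing baseline values, and the addendum and ethics re-review that the Ethics section requires for protocol changes. The listed covariates are already collected, so no new data are needed.

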## Methods/design

### Study design and settings

The study is designed as a randomized, placebo-controlled, multicentre trial, which will be conducted at four medical centres selected by the expert committee: the Huangshi Hospital of Traditional Chinese Medicine; Tongji Hospital, Tongji Medical College, Huazhong University of Science and Technology; LaoHeKou Traditional Chinese Medicine Hospital; and Leishenshan Hospital of Wuhan. A total of 300 participants fulfilling the eligibility criteria will be randomized into two groups (Baidu Jieduan granule group and control group) at a ratio of 1:1. The study flowchart is illustrated in Fig. 1. The Standard Protocol Items Recommendations for Interventional Trials (SPIRIT) checklist is presented in Additional file 1.

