### Interventions

The Baidu Jieduan granules are composed of 15 g of *Rheum palmatum L.* stem (*Dahuang*), 30 g of *Sargentodoxa cuneata (Oliv.) Rehd. et Wils.* (*Hongteng*), 30 g of *Taraxacum mongolicumHand.-Mazz.* (*Pugongying*), 45 g of *Raw Gypsum* (*Sheng Shigao*), 9 g of Herba Ephedra (*Mahuang*), 45 g of *Talcum* (*Huashi*), 12 g of *Amygdalus Communis Vas* (*Xingren*), 9 g of *Radix Glycyrrhizae (Gancao)*, 30 g of *Verbena officinalis L.* (*Mabiancao*), 30 g of *Polygonum cuspidatum* (*Huzhang*), 30 g of *Scutellariae Radix* (*Huangqin*) and 12 g of *Bombyx batryticatus* (Jiangchan), packaged in two bags. The Baidu Jieduan granules will be administered orally two times a day for 14 days. The Baidu Jieduan granules are manufactured by Beijing Tcmages Pharmaceutical Co., Ltd. (number: Jing 20180032).

The participants will be categorized into two groups receiving either standard Western medicine alone according to the *Protocol for Diagnosis and Treatment of Novel Coronavirus Pneumonia* (7th edition) or the combination of Baidu Jieduan granules two times a day for 14 days plus standard care. Routine care includes early fluid resuscitation, antimicrobial anticoagulants, nutritional support and other treatments. Other TCM therapies, including TCM injections and other oral herbal medicines, will be prohibited.

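### The analysis set labelled intent-to-treat is defined by taking the granules and having follow-up: no control can meet it literally, and if controls are kept the intake condition can exclude patients from the granule arm only

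*Protocol article*

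**What the plan says.** The main analysis population is defined in one sentence of the Statistical analysis section, which begins: "All patients will be analysed on the basis of intent-to-treat analysis, including all randomized subjects who take Baidu Jieduan granules at least once". In full, the restriction reads "including all randomized subjects who take Baidu Jieduan granules at least once and have follow-up information recorded", so follow-up must also be on record. The next sentence gives the missing-data method: "In the case of missing data, multiple imputation will be carried out to generate missing values".

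The Interventions section describes the two arms. One is "receiving either standard Western medicine alone"; the other receives "the combination of Baidu Jieduan granules two times a day for 14 days plus standard care". Under Randomization and blinding the article states: "This will be an open-label study". The article gives no separate inclusion rule for control patients.

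**The concern.** Membership of an intent-to-treat set is settled by randomization alone. Here it depends on two things that happen afterwards: swallowing a first dose of the experimental product, and having follow-up recorded.

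The first condition cannot be met in the control arm. An analyst must therefore either produce a set without controls or rewrite the rule, possibly once data are in view. The natural rewrite keeps all controls and still drops granule patients who never start. Allocation is known before the first dose, so not starting may depend on prognosis or on knowledge of the assignment, and the control arm has no matching exclusion.

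The second condition works against the planned imputation, because patients with no follow-up leave the set before anything can be imputed for them.

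At stake are the validity of the main comparison and the accuracy of its label.

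**Working it through.** **Step 1. The rule set against the arms.**

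| Condition | Granule arm | Control arm |
|---|---|---|
| Took the granules at least once | can be met; never-starters fail | cannot be met (standard care alone) |
| Follow-up recorded | can fail | can fail |

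Taken literally, 0 of about 150 controls enter the set. The phrase in Study design and settings, "The study is designed as a randomized, placebo-controlled, multicentre trial", does not change this. No placebo is described, the Discussion says the trial is not placebo-controlled, and a placebo would not be Baidu Jieduan granules in any case.

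**Step 2. Size of the effect if controls are kept.** The plan gives no figure to reproduce on this point, so what follows is an illustration.

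Inputs from the article: 150 per arm (Sample size), two-sided 5% test (Statistical analysis), and a conventional-treatment rate of 61.1% (Sample size; a symptom-recovery rate, used only as one plausible value).

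Assumptions, not in the article: no true effect; a second response level of 75%; a fraction d = 5% or 10% of the granule arm never starting; a response q among never-starters. Only the intake condition is modelled.

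With true response p in both arms:

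- Observed granule rate: p_t = (p − d·q)/(1 − d), with n1 = 150(1 − d) against n2 = 150.
- Apparent difference: Δ = p_t − p.
- Pooled rate: p̄ = (n1·p_t + n2·p)/(n1 + n2).
- SE0 = √[p̄(1 − p̄)(1/n1 + 1/n2)] and SE1 = √[p_t(1 − p_t)/n1 + p(1 − p)/n2].
- Rejection probability: Φ((Δ − 1.96·SE0)/SE1) + Φ((−Δ − 1.96·SE0)/SE1).

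Worked case, p = 0.611, d = 0.10, q = 0: n1 = 135; p_t = 0.611/0.90 = 0.6789; Δ = 0.0679; p̄ = 0.6432; SE0 = 0.0568; SE1 = 0.0566. The rejection probability is 0.2209 + 0.0008 = 0.222.

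| p | q | d = 5%: Δ, type I error | d = 10%: Δ, type I error |
|---|---|---|---|
| 61.1% | 61.1% | 0, 5.0% | 0, 5.0% |
| 61.1% | 30% | +1.6 points, 6.0% | +3.5 points, 9.2% |
| 61.1% | 0% | +3.2 points, 8.7% | +6.8 points, 22.2% |
| 75% | 75% | 0, 5.0% | 0, 5.0% |
| 75% | 30% | +2.4 points, 7.6% | +5.0 points, 17.0% |
| 75% | 0% | +3.9 points, 12.5% | +8.3 points, 40.5% |

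**Step 3. Direction.** If never-starters do better than average, the sign reverses. With p = 75% and q = 90%, Δ = (0.75 − 0.045)/0.95 − 0.75 = −0.8 points at d = 5%, and (0.75 − 0.09)/0.90 − 0.75 = −1.7 points at d = 10%.

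**The case against.** Three parts of the opposing case stand.

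- **A set without controls is a drafting slip, not a plan.** A reader might infer that the trial would analyse no controls. The sentence opens by saying all patients are analysed, and the section goes on to between-group tests, so the documents do not support that inference. The literal reading shows that the rule is badly worded; it does not predict the analysis.
- **The exclusion is not wholly one-sided.** A reader might infer that both conditions act on the granule arm only. The follow-up condition applies to either arm. It also removes only patients with no follow-up at all. Under Patient withdrawal, data collected before withdrawal stay in the database, so imputation still covers patients with partial data. For patients with nothing after baseline, imputation would rest on baseline data alone.
- **Direction and size are not established.** A reader might infer that the rule favours the granules and raises the type I error to 40%. The article gives neither the proportion of never-starters nor their prognosis, and Patient withdrawal lists deterioration and recovery together as grounds for unsuitability. The 40% needs a 75% response, 10% never starting and no response in any of them. The 10% allowance under Sample size covers all withdrawal and loss to follow-up, not failure to start. Never-starting may be uncommon, since nurses dispense the drug and visits are timed by day of hospitalization. With 2% never starting and none responding, the type I error is about 6% at either response level.

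What does not stand is leaving the sentence alone. The wording is explicit, so a fuller analysis plan would have to contradict it rather than complete it.

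**Conclusion.** The definition is wrong as written and must be changed. That conclusion needs no numerical assumption: the stated set is not intent-to-treat, no control can meet it, and under the sensible reading its intake condition acts on one arm only, in an open-label trial.

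The consequence is a comparison that can be biased: in favour of the granules if never-starters have a worse prognosis, against them if they have a better one, and not at all if they respond like everyone else. The type I errors in the working run from the nominal 5% to about 22% at the article's 61.1% rate, and to about 40% at an assumed 75%. The upper ends come from the extreme case of no response among never-starters. These figures show sensitivity; they are not estimates for this trial, and the verdict does not rest on them.

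**What to change.** Replace the definition with one sentence: the primary analysis set is all randomized patients, analysed in the group assigned, whatever treatment they took and whether or not follow-up exists, with missing outcomes handled by the planned multiple imputation. Keep the condition of at least one dose only for the safety or per-protocol description of the granule arm.

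The cost is one sentence in the protocol or the analysis plan. Sample size, visits and treatment are unaffected. The estimate may become slightly less favourable to the granules.
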